#### GAIN Acceptability Survey Participants

An additional acceptability survey was offered to a subgroup of participants beginning in May 2023. A small number of participants were not offered participation for a variety of reasons (eg, study staff forgot, the participant had a complicated visit, and it was logistically best to not offer an additional component). We delayed the offer of acceptability surveys until after the study had been enrolling for approximately 1 year.

At the study visit, study staff offered participants the optional extra survey. Participants who expressed willingness to take the extra survey were emailed a link to the REDCap CASI within 3 days of their study visit. For people with HIV at Madison Clinic, we also began offering the survey immediately after the study visit on a study tablet or laptop to increase access for participants with limited email or internet.

The CASI asked questions about the acceptability of the POC NAT and result delivery. Participants testing for HIV received a survey that included questions on PrEP use and sexual history, and a set of 12 discrete-choice questions about HIV testing preferences (Multimedia Appendix 3). People with HIV received questions on POC NAT acceptability, ART use, viral load testing and cutoff levels, and undetectable = untransmittable (Multimedia Appendix 4). People with HIV at Madison Clinic also received questions about their provider and the delivery of the adherence counseling intervention (Multimedia Appendix 5). Because of the sensitive nature of some of the questions, the survey instructions recommended that participants take the survey in a private setting. The CASI was designed to take about 10 minutes, and participants were sent a US $10 gift card via email or received US $10 cash following survey completion.

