#### Recruitment Strategies

Participants were screened and approached regarding participation by study staff or provider referral. Patients at Madison Clinic could be called via phone in advance by study staff after chart review for eligibility, and patients at both sites were approached in the waiting room about study participation. A “priority score” was also developed using demographic and behavioral questions from a Center intake form for use in prioritizing clients at the Center for PrEP care and the GAIN study. Development and implementation of this priority score will be described separately.

For participants seeking HIV testing from the Center, we prioritized clients with a reactive POC antibody HIV test, those with any symptoms of AHI, and those who scored high on the priority score. For participants seeking HIV at Madison Clinic, we prioritized enrollment of patients seeking HIV testing and those seeking nPEP. Our recruitment target for these groups was 700 clients from the Center and 150 patients at Madison Clinic.

We aimed to recruit all people with HIV seeking STI testing at the Center. For people with HIV at Madison Clinic, we prioritized patients with low adherence and/or detectable viremia. Study staff attempted to conduct the study visit for these participants before their regular clinic visit, to initiate the POC NAT as soon as possible and maximize the chance that the participant might still be in clinic to receive their result in person. Our recruitment target for these groups was 50 clients at the Center and 212 patients at Madison Clinic.

Participants were invited during their study visit to participate in the extra survey and interview immediately after the study visit or on a later date. Our recruitment target for survey participation was 50 participants seeking HIV testing at each site and 50 people with HIV at each site. Our recruitment target for interview participation was 20 total participants seeking testing (at either site) and 20 total participants with HIV (at either site).

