#### GAIN Participants With HIV in the Madison Clinic RCT

Participants in the RCT signed a release of information and completed the linking survey and study visit survey as described above [36]. Then participants in this group were randomized by 1:1, variable-block-size randomization to either receive either the clinic standard of care or the standard of care plus the SAMBA Semi-Q and tailored counseling.

Beginning in April 2023, study staff also performed venipuncture for participants in both arms and drew a 10 mL EDTA tube for a study laboratory NAT and, if possible, for the convenience of the participant, any additional tubes for clinical purposes. This change was made to ensure that all persons had an FDA-approved NAT that could be used as the primary way to guide clinical decision-making.

For participants in both arms, study staff obtained follow-up data from ITHS to monitor patient outcomes for 1 year after the study visit. Viral loads were obtained from the standard-of-care group at the time of the study visit and through up to 1 year of follow-up so that time to virologic suppression could be compared between the 2 arms.

For participants randomized to the intervention arm, study staff also conducted a fingerstick and initiated the SAMBA Semi-Q. After the study procedures were completed, study staff connected the participant with their care team to complete their clinic visit. When the SAMBA Semi-Q result was ready, study staff delivered the result to the participant’s physician. When participants were still in the clinic, the physician delivered the result along with the brief adherence counseling intervention developed for the study in collaboration with clinic providers, the process for which has already been described (Multimedia Appendices 1 and 2) [36]. For participants who had left the clinic, the physician followed up with the patient either via phone or by EMR message, whichever was considered most appropriate. For each participant randomized to the POC NAT arm, the physician reported to the research study whether they discussed the POC NAT result with the participant in person, via phone, or not at all. SAMBA Semi-Q and research laboratory NAT results were manually entered into the EMR by the research team.

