Data from Aim 4 will contribute to a paper on the acceptability of POC NAT among persons testing for HIV, anticipated in 2026 (Table 7). Another paper will address the acceptability of POC NAT among people with HIV using both qualitative data from interviews and participant survey responses, anticipated in 2026. Another paper using data collected as part of Aim 4 activities will explore HIV testing preferences using both the acceptability survey and interview data. We will use a convergent parallel mixed methods design for integration of qualitative and quantitative data. For the interview sample size, we planned to conduct 20 interviews each among the HIV testing group and people with HIV, or until saturation of themes. For surveys, a sample size of 100 HIV testing participants and 100 people with HIV was determined based on feasibility, the literature, and consultation with a choice-modeling expert. We hypothesize that more than 80% of participants surveyed will report a positive experience with POC NAT and that SAMBA implementation will be acceptable in community- and clinic-based settings. However, we hypothesize that the 2-hour TAT will be a limitation to the feasible implementation of POC NAT and that the semiquantitative nature of the test and the limit of detection of 1000 copies/mL may cause some hesitation in the use of the SAMBA Semi-Q.

**Table 7. T7:** Planned publication topics, analyses, and timelines.

Anticipated publication topics	Contributing aims and sites	Planned analysis	Target sample size	Attained sample size	Anticipated publication date
Performance of SAMBA Qual for HIV Testing	Aim 1, Seattle’s LGBTQ+ Center and Madison Clinic	Laboratory and POC^a^ NAT^b^ concordance	850 study visits	550 study visits	2027
Impact of POC NAT on time to undetectable viral load and SAMBA Semi-Q performance	Aim 3, Madison Clinic	Survival analysis, laboratory, and POC NAT concordance	212 study visits with up to 1-year longitudinal follow-up	194 study visits	2026
Acceptability of POC NAT among persons testing for HIV	Aim 4 interviews, Seattle’s LGBTQ+ Center and Madison Clinic	Qualitative	20 or until saturation of themes	21 interviews	2026
HIV testing preferences	Aim 4 interviews and surveys, Seattle’s LGBTQ+ Center and Madison Clinic	Qualitative, discrete choice analysis	20 or until saturation of themes, 100 surveys	21 interviews, 143 surveys	2026

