### Limitations

The GAIN study has limitations that should be noted. Baseline data and prospective data collected from Madison Clinic and Center datasets could be incomplete because data were deidentified when transferred to the study team and might not perfectly reflect the participants recruited into the study. However, the study team worked closely with data managers from both sites to achieve as complete a dataset as possible. For study visits and follow-up interviews, only participants who spoke English were enrolled, excluding individuals with limited English proficiency. Poststudy survey and interview contact occurred primarily via email, which led to lower uptake and likely excluded participants without access to email. We modified our process in 2024 to allow these activities to be completed in person immediately after the study visit and provided cash reimbursement, which enabled some inclusion of participants without internet access. Though the original proposed protocol called for a comparison of multiple POC NATs, because of challenges with suppliers, the study team was not able to procure any other POC NATs for comparison. Future studies of POC NATs could assess other testing platforms.

Additional analyses based on the GAIN study protocol described here are planned and in progress. Future reports will include papers on the acceptability of the POC NAT among participants seeking HIV testing and people with HIV based on survey and interview results, an assessment of participant HIV testing preferences based on survey and interview results, an assessment of the impact of POC NAT on time to viral suppression, evaluations of the performance of POC NAT in comparison with laboratory NAT, and a final set of Madison Clinic time-and-motion data. Additional POC NAT implementation studies in US settings are needed to assess the acceptability and feasibility of this technology.

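### The on-site acceptability survey for people with HIV at Madison Clinic can come before the POC NAT result and counseling that some of its items ask about, and nothing ties its timing to result delivery

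*Protocol article*

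**What the plan says.** **Order of events in the Madison Clinic trial.** Under Recruitment Strategies: "Study staff attempted to conduct the study visit for these participants before their regular clinic visit, to initiate the POC NAT as soon as possible". The section on participants with HIV in the Madison Clinic RCT describes the POC NAT arm: fingerstick, start of the SAMBA Semi-Q, then "After the study procedures were completed, study staff connected the participant with their care team to complete their clinic visit". When the result is ready it goes to the physician, who gives it with brief adherence counseling if the participant is still in clinic. Otherwise the physician follows up by phone or record message. The physician also reports whether the result was discussed in person, by phone or not at all.

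**Survey timing.** The default route is email: participants who agreed "were emailed a link to the REDCap CASI within 3 days of their study visit". For one group a second route was added: "For people with HIV at Madison Clinic, we also began offering the survey immediately after the study visit on a study tablet or laptop". The Limitations section dates this change to 2024, when the process was modified to "allow these activities to be completed in person immediately after the study visit".

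**Survey content.** The instrument covers acceptability of the POC NAT and result delivery. Madison participants with HIV "also received questions about their provider and the delivery of the adherence counseling intervention".

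**Use of the answers.** The Results section hypothesizes that "more than 80% of participants surveyed will report a positive experience with POC NAT".

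**The concern.** Read in sequence, these sections put the on-site survey at the end of the research procedures. Result delivery and counseling come later in the attendance, or after the participant has gone home. A POC NAT arm respondent surveyed on site may therefore be asked about a result and a conversation that have not yet taken place. A positive rating from that person would describe the blood collection and the expectation of a result, not the experience of receiving one.

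Two features make this more than untidy. First, the usefulness of a test with a 2-hour turnaround depends on whether and how the result reaches the patient, so these items are close to the heart of the acceptability question. Second, the on-site route was added for participants with limited email or internet. If survey timing differs by route, any difference in answers is mixed up with that characteristic.

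**Working it through.** The plan has no figure of its own to reproduce here. The check is of order and of timing.

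**Inputs**
- Test turnaround: up to 120 minutes (POC NAT Selection).
- Total clinic time, including waiting room (Table 6): 2021 median 73, IQR 54 to 92, n = 25; 2023 median 64, IQR 45 to 88, n = 22.
- Surveys completed by people with HIV: 47 of 77 invited at Madison and MOD Clinics, 3 at the Center (Table 5).
- Arms: 97 standard of care, 97 POC NAT (Table 4).
- Minutes from fingerstick to start of the clinic visit: not given. Assumed range 0 to 60.

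**Step 1, narrow reading.** If the study visit means the research procedures only, and it is held before the clinic visit, the sequence is: fingerstick, on-site survey, clinic visit, result and counseling. The survey precedes all the later events.

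**Step 2, broad reading.** Suppose the study visit loosely covers the whole attendance, so that the survey follows the clinic visit. With no head start, the result is still pending at the median by 120 − 73 = 47 minutes (2021) and 120 − 64 = 56 minutes (2023).

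**Step 3, effect of an earlier start.** As an illustration, fit a lognormal to each median m and IQR, with s = [ln(Q3) − ln(Q1)] / (2 × 0.6745). This gives s = ln(92/54)/1.349 = 0.395 for 2021 and s = ln(88/45)/1.349 = 0.497 for 2023. The share of clinic visits lasting until the result, given a head start of h minutes, is 1 − Φ([ln(120 − h) − ln m]/s).

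| Head start (assumed) | 2021 | 2023 |
|---|---|---|
| 0 min | 10% | 10% |
| 30 min | 30% | 25% |
| 60 min | 69% | 55% |

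On the broad reading the result is thus still pending when the clinic visit ends for about 90% of visits with no head start, 70% to 75% with 30 minutes, and 31% to 45% with 60 minutes. These are rough figures from small samples. The 2023 total IQR in Table 6 is also wider than the IQR of either clinic (61 to 74 and 51 to 80), so the 2023 spread is uncertain. The 2021 data give the same picture.

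**Step 4, weight of one survey.** Madison supplies 47 of the 50 surveys from people with HIV (94%) and 47 of all 193 (24%). One survey is 1/47 = 2.1 percentage points of the Madison figure. Only the POC NAT arm receives a result. If respondents split evenly by arm (an assumption, since the split is not reported), about 47/2 = 23.5 are relevant and one survey is worth about 1/23.5 = 4.3 points.

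**The case against.** **The order is inferred.** The article never defines when a study visit ends, and holding it before the clinic visit was only attempted. Some participants may have waited for the result and then taken the survey. This stands. It rules out saying that on-site surveys always came first, but not that they could, because no sentence makes the survey wait.

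**The instrument is not shown.** The survey appendices may contain skip logic or a not-yet-received option. This stands too. A reader might infer that respondents were made to describe events that had not happened; the article does not establish that.

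**The number affected is unknown.** Any count of on-site surveys would be a guess. The route dates from 2024, whereas surveys began in May 2023, and the standard-of-care arm is due no POC result at any time. A share of all 47 would therefore overstate the exposure.

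**Email is not a clean comparator.** The link came within 3 days. Physician follow-up after departure had no stated deadline and might not happen at all, so emailed surveys can also precede or lack delivery. This stands, and it argues for classifying every survey by delivery status rather than by route.

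**The one-hour figure for research and clinic procedures does not apply.** It comes from the section on testing participants and Center participants with HIV. It is not used above.

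**The consequence is limited.** The planned analysis for this group is qualitative and descriptive, the 80% hypothesis spans all survey groups, and items on ART use, viral load cutoffs and undetectable = untransmittable do not depend on order. All true. But a separate paper on people with HIV is planned, and Madison supplies nearly all its surveys.

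**Conclusion.** The concern holds in a limited form. As written, the on-site survey can precede the POC NAT result and the counseling that some of its items cover, and the article contains no rule preventing this. The exposure is confined to POC NAT arm respondents at Madison Clinic and to the items on POC NAT experience, result delivery and counseling.

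Its size cannot be stated, because neither the on-site count nor the arm split of the 47 surveys is reported. On the narrow reading every on-site survey in that arm is early. On the broad reading a sizeable share could still be, depending on the assumed head start. The documents do not support the stronger inference that on-site answers as a whole are invalid or that the 80% hypothesis cannot be assessed. The time-to-suppression analysis and its sample size are untouched.

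**What to change.** Enrollment has ended, so the useful change is to the acceptability analysis anticipated in 2026.

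1. Classify every POC NAT arm survey from Madison Clinic, on-site or emailed, as completed before or after result delivery. Use survey completion time (assuming REDCap kept it), SAMBA result time and the physician's delivery report.
2. The article describes the delivery report as recording how the result was discussed, not when. Keep an undetermined class for surveys completed after the result was ready but without a datable delivery. Surveys completed before the result time are early without further evidence.
3. Treat result-delivery and counseling items as not applicable where the result had not been delivered.
4. Compute the positive-experience figure for people with HIV at Madison Clinic from post-result surveys. Show pre-result and undetermined surveys separately, with counts by route.
5. State in the paper when the study visit ended relative to the clinic visit, and whether the instrument had a not-yet-received option.

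The cost is one derived variable, largely from data already collected, and a smaller denominator with wider uncertainty for the affected items. If few surveys prove early, the classification will show that and the matter closes.

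The article offers this protocol as a model for later studies. For that use, the on-site survey should be offered only after the result has been delivered.

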#### GAIN Participant Interviews

From June through November 2023, all participants who completed the postvisit acceptability survey were invited to complete a semistructured interview with study staff either in person, via phone, or via Zoom (Zoom Video Communications, Inc.). Participants were contacted via email, and study staff attempted to schedule interviews within 1 month of the participant’s study visit to maximize recall. The conversations were audio-recorded and transcribed by HIPAA (Health Insurance Portability and Accountability Act)–compliant Global Marketing Resources (GMR) Transcription. Once the transcripts were reviewed for accuracy and any identifying information was removed, the original recordings were deleted.

The topics covered in the interviews included more detailed, open-ended questions about the acceptability of the POC NAT and result delivery and, for participants who tested HIV-negative, a discussion of their HIV testing preferences (Multimedia Appendix 6). People with HIV were asked about viral load monitoring and their care preferences, viral load cutoff levels, and undetectable = untransmittable, and the adherence intervention conversation with their provider (Multimedia Appendices 7 and 8).

When thematic saturation appeared to have been reached for participants who tested HIV-negative, recruitment continued until February 2024 only for participants who tested HIV-negative who were persons of color or transgender, in order to increase the diversity of the sample. These interviews continued with people with HIV through the duration of the study.

#### GAIN Provider Interviews

We also interviewed providers at Madison Clinic to obtain input on the acceptability and feasibility of POC NAT use in the clinical setting from the provider perspective. In a first round of preimplementation key informant interviews with providers at Madison Clinic, we explored perspectives on the possible utility of POC NAT and integration into clinic flow. We also solicited provider input on the development of an ultra-brief adherence counseling intervention using motivational interviewing and problem-solving counseling techniques, the results of which have been described elsewhere [36]. Brief, postimplementation interviews were conducted with providers who successfully delivered a POC NAT result to a participant to gain insight into the process of test result delivery and adherence counseling. More formal interviews are planned at the completion of the project to solicit feedback on the utility of the SAMBA Semi-Q.

#### GAIN Time and Motion Observations

Time-and-motion studies were conducted at three times: February-July 2021 before study enrollment began to inform study implementation, March-April 2023 for a post-COVID pandemic repeat assessment (during a regulatory study pause in enrollment), and November 2023 to October 2024 during study enrollment to assess the impact of the POC NAT on clinic flow [37]. Patients were observed by study staff from the time they arrived in the waiting room until they departed the clinic, with staff noting the type of visit and the time of each subsequent segment of the patient visit (eg, front desk check-in, waiting room time, and time the patient spent with each provider type). The final time-and-motion dataset conducted during study enrollment also noted participant time spent on research procedures. That final dataset evaluating the impact of POC NAT implementation will be reported elsewhere.

### Data Collection and Statistical Analysis

GAIN study data sources are shown in Table 1. We present demographic data for client visits in the baseline dataset and GAIN participants in Tables 2-4 as descriptive statistics. When data from the study visit survey were missing, we filled in missing values whenever possible with EMR data. Demographic data are presented at the participant level and include gender, race, insurance, and PrEP and ART status. Planned statistical analyses are described with anticipated timelines for completion.

**Table 1. T1:** Data sources for the Greater Access and Impact through Point-of-Care Nucleic Acid Test study.

Dataset	Source	Participants	Data included
Baseline data from Seattle’s LGBTQ+^a^ Center	Seattle’s LGBTQ+ Center InSync EMR^b^, Google Forms intake	Preimplementation, nonstudy participants	Demographics, HIV POC^c^ and laboratory test results, PrEP^d^ prescriptions
Baseline data from Madison Clinic	Madison Clinic Epic EMR, PrEP PRO^e^	Preimplementation, nonstudy participants	Demographics, HIV POC and laboratory test results, PrEP visits, viral load results, and AR^f^T medications
Linking survey	REDCap^g^, study staff completed at the study visit	All participants	Patient EMR, Study ID, name, date of birth, and contact information
Study visit survey	REDCap, participant completed at the study visit	All participants	Patient demographics, substance use, and ART use
Test results	REDCap, study staff completed at the study visit and after the study visit	All participants	POC and laboratory HIV test results
Follow-up phone calls	REDCap, study staff completed after the study visit	All participants at Seattle’s LGBTQ+ Center	PrEP initiation, ART use, viral load results, and connection to HIV care
Follow-up acceptability survey	REDCap, participant completed after the study visit	Subset of all participants	POC NAT^h^ perspectives, PrEP preferences, and viral load testing preferences
Follow-up in-depth interview	Qualitative interview conducted after the study visit	Subset of participants completing the acceptability survey	POC NAT perspectives, PrEP preferences, and viral load testing preferences
Prospective data from Seattle’s LGBTQ+ Center	Seattle’s LGBTQ+ Center InSync EMR, Google Forms intake	All participants at Seattle’s LGBTQ+ Center	Demographics, HIV POC and laboratory test results, and PrEP prescriptions
Prospective data from Madison Clinic	Madison Clinic Epic EMR, PrEP PRO	All participants at Madison Clinic	Demographics, HIV POC and laboratory test results, PrEP visits, viral load results, and ART medications
Time and motion data	Observational data on patient flow through Madison Clinic collected by study staff	Nonparticipants, Madison participants with HIV	Timing of clinic and study visit components

a LGBTQ+: lesbian, gay, bisexual, transgender, queer, and others.

b EMR: electronic medical record.

c POC: point-of-care.

d PrEP: pre-exposure prophylaxis.

e PRO: patient-reported outcomes.

f ART: antiretroviral therapy

g REDCap: Research Electronic Data Capture

h NAT: nucleic acid test.

**Table 2. T2:** Characteristics of baseline visits by clients at Seattle’s LGBTQ+^a^ Center (January 2019-December 2021) and participants in the GAIN^b^ study who were seeking HIV and STI^c^ testing and PrEP^d^ (January 2022-August 2024).

Characteristic	Baseline client visits (Jan 2019-Dec 2021)			GAIN^b^ study participant visits	
	HIV and STI^c^ testing visits	PrEP^d^ visits	Total visits	Visits by participants seeking HIV testing and PrEP (Jan 2022- Aug 2024)	Visits by participants with HIV seeking STI testing (Mar 2022-Aug 2024)
Total, n (%)	6906 (96.2)	272 (3.8)	7178 (100)	489 (100)	7 (100)
Age (years), median (IQR)	30 (26-38)	28 (24-33)	30 (26-37)	30 (25-35)	57 (41-61)
Gender, n (%)					
Cisgender man	5487 (79.5)	216 (79.4)	5703 (79.5)	333 (68.1)	7 (100)
Cisgender woman	430 (6.2)	0 (0.0)	430 (6.0)	35 (7.2)	0 (0)
Transgender man	99 (1.4)	2 (0.7)	101 (1.4)	13 (2.7)	0 (0)
Transgender woman	190 (2.8)	13 (4.8)	203 (2.8)	17 (3.5)	0 (0)
Nonbinary or genderqueer (AMAB^e^)	307 (4.4)	14 (5.1)	321 (4.5)	51 (10.4)	0 (0)
Nonbinary or genderqueer (AFAB)^f^	206 (3.0)	1 (0.4)	207 (2.9)	30 (6.1)	0 (0)
Nonbinary or genderqueer (another gender or intersex at birth, missing sex at birth)	18 (0.3)	0 (0.0)	18 (0.3)	6 (1.2)	0 (0)
Missing	169 (2.4)	26 (9.6)	195 (2.7)	4 (0.8)	0 (0)
Race or ethnicity, n (%)					
American Indian or Alaska Native	40 (0.6)	2 (0.7)	42 (0.6)	1 (0.2)	0 (0)
Asian	1015 (14.7)	26 (9.6)	1041 (14.5)	69 (14.1)	0 (0)
Black or African American	628 (9.1)	34 (12.5)	662 (9.2)	28 (5.7)	0 (0)
Native Hawaiian or Other Pacific Islander	75 (1.1)	10 (3.7)	85 (1.2)	2 (0.4)	1 (14.3)
White	3375 (48.9)	77 (28.3)	3452 (48.1)	278 (56.9)	5 (71.4)
Latinx^g^	1194 (17.3)	77 (28.3)	1271 (17.7)	72 (14.7)	1 (14.3)
Multiracial^h^	451 (6.5)	16 (5.9)	467 (6.5)	36 (7.4)	0 (0)
Middle Eastern or South Asian	37 (0.5)	2 (0.7)	39 (0.5)	ND^i^	ND
Missing or no response	91 (1.3)	28 (10.3)	119 (1.7)	3 (0.6)	0 (0)
Insurance, n (%)					
Public insurance	391 (5.7)	27 (9.9)	418 (5.8)	87 (17.8)	2 (28.6)
Private insurance	1663 (24.1)	46 (16.9)	1709 (23.8)	250 (51.1)	5 (71.4)
Unspecified type	2648 (38.3)	0 (0.0)	2648 (36.9)	11 (2.2)	0 (0)
No insurance	2138 (31.0)	47 (17.3)	2185 (30.4)	121 (24.7)	0 (0)
Not sure or missing	66 (1.0)	152 (55.9)	218 (3.0)	20 (4.3)	0 (0)
Substance use, n (%)					
IDU^j^ (past year)^k^	224 (3.4)	12 (11.1)	236 (3.5)	ND^i^	ND
IDU (past 3 mo)	ND	ND	ND	4 (0.8)	0 (0)
Meth (past 3 mo)^l^	65 (2.1)	6 (5.2)	71 (2.2)	13 (2.7)	0 (0)
HIV status and PrEP or ART^m^ use, n (%)					
HIV negative	5937 (86.0)	N/A^n^	N/A	489 (100)	0 (0.0)
Currently on PrEP	929 (15.6)	N/A	N/A	123 (25.5)	N/A
HIV positive	175 (2.5)	N/A	N/A	0 (0)	7 (100)
Currently on ART	55 (31.4)	N/A	N/A	N/A	6 (85.7)
Not currently on ART	15 (8.6)	N/A	N/A	N/A	1 (14.3)
ART status unknown or missing	105 (60.0)	N/A	N/A	N/A	0 (0)
HIV status unknown or missing	794 (11.5)	N/A	N/A	0 (0)	0 (0)

a LGBTQ+: lesbian, gay, bisexual, transgender, queer, and others.

b GAIN: Greater Access and Impact through Point-of-Care Nucleic Acid Test.

c STI: sexually transmitted infection.

d PrEP: pre-exposure prophylaxis.

e AMAB: assigned male at birth

f AFAB: assigned female at birth.

g Participants who selected Latinx and any other race were categorized as Latinx.

h Participants who selected any 2 or more races but not Latinx were categorized as multiracial.

i ND: no data available; data that was not collected for the group listed.

j IDU:

k Asked of 6575 test participants and 108 PrEP participants.

l Asked of 3107 test participants and 108 PrEP participants.

m ART: antiretroviral therapy

n N/A: not applicable; variable does not apply to the group listed.

**Table 3. T3:** Characteristics of baseline visits from patients at Madison Clinic (Jan 2019-Dec 2021) and participants in the GAIN^a^ study seeking HIV and STI^b^ testing, nPEP^c^, or PrEP^d^ (January 2022-August 2024).

Characteristic	Baseline patient visits (January 2019-December 2021)				GAIN^a^ study participant visits (Jan 2022-Aug 2024)
	nPEP visits	HIV testing visits	PrEP visits	Total visits	HIV and STI testing, nPEP, and PrEP visits
Total, n (%)	117 (13.8)	328 (38.8)	400 (47.3)	845 (100)	43 (100)
Age (years), median (IQR)	31 (26-39)	32 (27-42)	33 (27-44.5)	33 (27-43)	35 (31-44)
Gender, n (%)					
Cisgender man	117 (100)	177 (54)	348 (87)	642 (76)	37 (86)
Cisgender woman	0 (0)	150 (45.7)	51 (12.8)	201 (23.8)	1 (2.3)
Transgender man	0 (0)	0 (0)	0 (0)	0 (0)	0 (0)
Transgender woman	0 (0)	0 (0)	0 (0)	0 (0)	2 (4.7)
Nonbinary or genderqueer (AMAB^e^)	0 (0)	0 (0)	0 (0)	0 (0)	1 (2.3)
Nonbinary or genderqueer (AFAB^f^)	0 (0)	0 (0)	0 (0)	0 (0)	0 (0)
Nonbinary (unknown sex at birth)	0 (0.0)	1 (0.3)	1 (0.3)	2 (0.2)	0 (0.0)
Another gender identity	0 (0.0)	0 (0.0)	0 (0.0)	0 (0.0)	2 (4.7)
Missing	0 (0.0)	0 (0.0)	0 (0.0)	0 (0.0)	0 (0.0)
Race or ethnicity, n (%)					
American Indian or Alaska Native	1 (0.9)	3 (0.9)	10 (2.5)	14 (1.7)	0 (0.0)
Asian	20 (17.1)	33 (10.1)	36 (9.0)	89 (10.5)	2 (4.7)
Black or African American	12 (10.3)	44 (13.4)	25 (6.3)	81 (9.6)	2 (4.7)
Hispanic or Latinx^g^	20 (17.1)	13 (4.0)	40 (10.0)	73 (8.6)	11 (25.6)
Native Hawaiian or Other Pacific Islander	1 (0.9)	1 (0.3)	2 (0.5)	4 (0.5)	1 (2.3)
White	51 (43.6)	178 (54.3)	198 (49.5)	427 (50.5)	27 (62.8)
Multiracial^h^	1 (0.9)	7 (2.1)	11 (2.8)	19 (2.2)	0 (0.0)
Missing or no response	11 (9.4)	49 (14.9)	78 (19.5)	138 (16.3)	0 (0.0)
Insurance, n (%)					
Public insurance	39 (33.3)	94 (28.7)	121 (30.3)	329 (38.9)	19 (44.2)
Private insurance	55 (47.0)	125 (38.1)	149 (37.3)	254 (30.1)	16 (37.2)
Another insurance	5 (4.3)	62 (18.9)	75 (18.8)	142 (16.8)	0 (0.0)
Missing	18 (15.4)	47 (14.3)	55 (13.8)	120 (14.2)	9 (20.9)
PrEP use (reported by participant), n (%)					
Never	ND^i^	ND	ND	ND	7 (16.3)
Previously	ND	ND	ND	ND	6 (14.0)
Currently	ND	ND	ND	ND	30 (69.8)
Missing	ND	ND	ND	ND	0 (0.0)
Reason for visit (reported by study staff), n (%)					
HIV testing	ND	ND	ND	ND	6 (14.0)
PEP	ND	ND	ND	ND	6 (14.0)
PrEP start	ND	ND	ND	ND	5 (11.6)
PrEP persistence	ND	ND	ND	ND	26 (60.5)

a GAIN: Greater Access and Impact through Point-of-Care Nucleic Acid Test.

b STI: sexually transmitted infection.

c nPEP: nonoccupational postexposure prophylaxis.

d PrEP: pre-exposure prophylaxis.

e AMAB: assigned male at birth.

f AFAB: assigned female at birth

g Participants who selected Latinx and any other race were categorized as Latinx.

h Participants who selected any 2 or more races but not Latinx were categorized as multiracial.

i ND: no data available; data that wasn’t collected for this variable for this group

**Table 4. T4:** Characteristics of baseline visits by patients at Madison Clinic (Jan 2019-Dec 2021) and GAIN^a^ study participants living with HIV (Jan 2022-Aug 2024).

Characteristics	Baseline visits by patients at Madison Clinic (Jan 2019-Dec 2021)			GAIN^a^ study visits (Jan 2022-Aug 2024)
	Patients with first reactive HIV result	Patients with detectable HIV viral load	Total patients	Participants with HIV
Total, n (%)	146 (22.2)	511 (77.8)	657 (100)	194 (100)
Age (years), median (IQR)	34 (28‐47)	43 (32‐52)	41 (31‐51)	44.5 (35-57)
Gender, n (%)				
Cisgender man	117 (80.1)	406 (79.5)	523 (79.6)	144 (74.2)
Cisgender woman	29 (19.9)	104 (20.4)	133 (20.2)	19 (9.8)
Transgender man	0 (0.0)	0 (0.0)	0 (0.0)	0 (0.0)
Transgender woman	0 (0.0)	0 (0.0)	0 (0.0)	10 (5.2)
Nonbinary or genderqueer (AMAB)^b^	0 (0.0)	0 (0.0)	0 (0.0)	15 (7.7)
Nonbinary or genderqueer (AFAB)^c^	0 (0.0)	0 (0.0)	0 (0.0)	0 (0.0)
Nonbinary or genderqueer (unknown sex at birth)	0 (0.0)	1 (0.2)	1 (0.2)	0 (0.0)
Another gender identity	0 (0.0)	0 (0.0)	0 (0.0)	6 (3.1)
Missing	0 (0.0)	0 (0.0)	0 (0.0)	0 (0.0)
Race or ethnicity, n (%)				
American Indian or Alaska Native	0 (0)	14 (2.7)	14 (2.1)	3 (1.6)
Asian	10 (6.8)	20 (3.9)	30 (4.6)	4 (2.1)
Black or African American	43 (29.5)	152 (29.7)	195 (29.7)	53 (27.3)
Hispanic or Latinx^d^	12 (8.2)	21 (4.1)	33 (5.0)	27 (13.9)
Native Hawaiian or Other Pacific Islander	1 (0.7)	8 (1.6)	9 (1.4)	5 (2.6)
White	56 (38.4)	239 (46.8)	295 (44.9)	84 (43.3)
Multiracial^e^	4 (2.7)	4 (0.8)	8 (1.2)	17 (8.8)
Missing or no response	20 (13.7)	20 (3.9)	40 (6.1)	1 (0.5)
Insurance, n (%)				
Public insurance	55 (37.7)	325 (63.6)	380 (29.8)	162 (83.5)
Private insurance	61 (41.8)	135 (26.4)	196 (57.8)	28 (14.4)
Another insurance	12 (8.2)	17 (3.3)	29 (4.4)	1 (0.5)
Missing	18 (12.3)	34 (6.7)	52 (7.9)	3 (1.6)
ART^f^ use, n (%)				
Never	ND^g^	ND	ND	38 (19.6)
Previously	ND	ND	ND	19 (29.4)
Currently	ND	ND	ND	134 (69.1)
missing	ND	ND	ND	3 (1.6)
Laboratory viral load, n (%)^h^				
Detectable (≥40 copies)	N/A^i^	N/A	N/A	63 (32.5)
Undetectable (<40 copies)	N/A	N/A	N/A	113 (58.2)
Laboratory viral load not done	N/A	N/A	N/A	18 (9.3)^j^
Randomization arm, n (%)				
Standard of care	N/A	N/A	N/A	97 (50)
Point-of-care NAT^k^	N/A	N/A	N/A	97 (50)

a GAIN: Greater Access and Impact through Point-of-Care Nucleic Acid Test.

b AMAB: assigned male at birth.

c AFAB: assigned female at birth.

d Participants who selected Latinx and any other race were categorized as Latinx.

e Participants who selected any 2 or more races but not Latinx were categorized as multiracial.

f ART: antiretroviral therapy

g ND: no data available; data that was not collected for the group listed.

h Filled in with clinic electronic medical record if available within 15 days of visit date when study VL not available.

i N/A: not applicable; variable does not apply to the group listed

j Laboratory viral load test was not done for participants enrolled before October 2022 (n=7) and for participants from whom no blood could be drawn due to hard stick (n=8). When available, viral load values were obtained from the clinic electronic medical record.

k NAT: nucleic acid test.

